### Outcome measures

#### Questionnaires

- Dizziness handicap inventory (DHI).

Time to fill out: 10 minutes.

The DHI is a widespread used self-report questionnaire, designed to quantify the impact of dizziness on everyday life. The DHI has 25 items with 3 answer categories ('yes', 'sometimes', or 'no'), investigating self-perceived physical, emotional, and functional disability associated with dizziness. DHI scores range from 0-100. A higher DHI score indicates a higher level of dizziness-related impairment. A DHI score of  $\geq 30$  correlates with current significant impairment because of dizziness.

- Dizziness handicap inventory, short version (DHI-S).

This is a short screening version of the DHI, in which 10 items of the original DHI are extracted. The 10 items in the DHI-S are scored are also scored in 3 answer categories ('yes', 'sometimes', or 'no'). A DHI score of  $\geq 12$  correlates with current significant impairment because of dizziness.

- Generalised Anxiety Disorder-7 (GAD-7).

Time to fill out: 5 minutes.

The GAD-7 is a 7-item questionnaire to identify GAD. Scores on the GAD-7 range from 0 to 21; scores of 5, 10, and 15 represent mild, moderate, and severe anxiety symptoms, respectively.

- Patient Health Questionnaire, panic module (PHQ-PD).

Time to fill out: 5 minutes.

The PHQ-PD will enable us to determine the presence of PD. The diagnostic algorithm for PD consists of 15 questions with 2 answer categories (yes or no) and is considered fulfilled if the answer to questions 3a-d is "yes" and if the answer to 4 or more of questions 4a-k is "yes".

- 9-item Patient Health Questionnaire depression module (PHQ-9).

Time to fill out: 5 minutes.

The PHQ-9 is designed to detect depression. The PHQ-9 has 9 questions with a score ranging from 0 to 3 for each question (maximum score of 27). A threshold score of 10 or higher is considered to indicate mild MDD, 15 or higher indicates moderate MDD, and 20 or higher severe MDD.

- Euro Quality of Life–5-dimension, 5-level (EQ-5D-5L).

Time to fill out: several minutes.

The EQ-5D-5L is a questionnaire that defines health in five dimensions (mobility, self-care, usual activities, pain/discomfort, anxiety/depression) and is often used to translate the effect of an intervention into Quality Adjusted Life Years (QALY's).

#### *Calendar*

- Dizziness and fall calendar for patients of group B and C (n = 250). At baseline assessment the patient will be handed out a calendar to keep up frequency dizziness and falls for 12 months. The patient will be instructed in the use of keeping up dizziness and fall frequency with the calendar. The patient will be asked to fill out the calendar every week which will take no more than 1 minute weekly.

The following table gives an overview of all measurements and instruments.

| Overview of all measurements and instruments |                  |       |        |                    |       |       |        |
|----------------------------------------------|------------------|-------|--------|--------------------|-------|-------|--------|
|                                              | Validation study |       |        | Intervention study |       |       |        |
|                                              | baseline         | 6 mo. | 12 mo. | baseline           | 3 mo. | 6 mo. | 12 mo. |
| Screening dizziness                          |                  |       |        |                    |       |       |        |
| handicap (DHI-S)                             | x                |       |        | x                  |       |       |        |
| Baseline assessment                          | x                |       |        | x                  |       |       |        |
| Dizziness Handicap (DHI)                     | x                | x     | x      | x                  | x     | x     | x      |
| QoL (EQ-5D-5L)                               | x                | x     | x      | x                  |       | x     | x      |
| Depression (PHQ-9)                           | x                | x     | x      | x                  | x     | x     | x      |
| Anxiety (GAD-7)                              | x                | x     | x      | x                  | x     | x     | x      |
| Panic disorder (PHQ-PD)                      | x                | x     | x      | x                  | x     | x     | x      |
| FRID count                                   | x                |       | x      | x                  |       |       | x      |
| Dizziness and fall frequency (calendar))     |                  |       |        | ----- weekly ----- |       |       |        |

#### **8.4 Withdrawal of individual subjects**

Subjects can leave the study at any time for any reason if they wish to do so without any consequences. The investigator can decide to withdraw a subject from the study for urgent medical reasons.

**8.4.1 Specific criteria for withdrawal (if applicable)**

Patients will be withdrawn from the study if they are diagnosed with severe cognitive impairment. Furthermore, patients participating in the intervention-arm 'exercise therapy' will be withdrawn from the intervention if the patients develops serious comorbid conditions that precludes participation in an exercise program.

**8.5 Replacement of individual subjects after withdrawal**

Patients will be asked to participate in the study until the sample-size for the study has been reached. Patients will not be replaced from intervention group to control group or vice versa.

**8.6 Follow-up of subjects withdrawn from treatment**

Patients who have withdrawn from treatment will be asked to keep up filling out the questionnaires since we aim to perform an intention-to-treat analysis. Furthermore, reason for drop out will be stored in the database to be able to perform a loss-to follow-up analysis if necessary.

**8.7 Premature termination of the study**

Not applicable.

## 9. SAFETY REPORTING

### 9.1 Section 10 WMO event

In accordance to section 10, subsection 1, of the WMO, the investigator will inform the subjects and the reviewing accredited METC if anything occurs, on the basis of which it appears that the disadvantages of participation may be significantly greater than was foreseen in the research proposal. The study will be suspended pending further review by the accredited METC, except insofar as suspension would jeopardise the subjects' health. The investigator will take care that all subjects are kept informed.

### 9.2 AEs, SAEs and SUSARs

#### 9.2.1 Adverse events (AEs)

Adverse events are defined as any undesirable experience occurring to a subject during the study, whether or not considered related to the experimental intervention. All adverse events reported spontaneously by the subject or observed by the investigator or his staff will be recorded.

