#### 1. Medication adjustment

Dizzy patients using  $\geq 3$  FRIDs will be subjected to a FRID-analysis. The list of FRIDs include psychotropic drugs (sedatives, antidepressants, neuroleptics), cardiovascular drugs (antihypertensives, nitrates, anti-arrhythmics, nicotinic acid,  $\beta$ -adrenoceptor blocker eye drops) and other drugs (analgesics, antivertigo preparations, hypoglycaemics, urinary antispasmodics). Interventional studies demonstrated a reduction in falls and postural instability following FRID-withdrawal.

All study patients will be asked about medication use during baseline assessment. After baseline assessment current prescribed medication will be requested from the patients pharmacist. The medication list will be sent by fax to the researcher. The patient will receive a phone call by the researcher for extra clarification if there is a discrepancy between the medication list supplied by the patient and the medication list supplied by the pharmacist.

Once a month, a trained pharmacist and an independent GP will have a meeting to review the FRID use of all patients of the intervention 'medication adjustment' that have been included in the preceding month. In every individual patient of group C, all potential FRIDs will be considered for withdrawal. If a FRID is considered redundant, the pharmacist and GP will advise to stop it. If a FRID is considered necessary, the pharmacist and GP will advise to change to another drug that sorts the same effect, or to reduce the dosage if considered safely possible. The results of the FRID-analysis, including considerations for

discontinuation/withdrawal of FRIDs, will be handed to the patients GP and practice nurse by fax. The practice nurse will invite the patient for a consultation with his/her GP within two weeks. The GP will discuss the outcomes of the FRID-analysis with the patient and will stop or withdrawal the FRIDs if the patient agrees. The GP will fill out a small questionnaire to give feedback about adjustment of medication to researcher.

If discontinuation or withdrawal of FRID appears to be impossible, the GP and the patient will receive a letter of the researcher.

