## 2. Stepped-care for anxiety/depression

Dizzy older patients with the risk factor 'anxiety and/or depression' (defined as the presence of Generalised Anxiety Disorder (GAD), Panic Disorder (PD), or Major Depressive Disorder (MDD)), will follow a stepped-care program, according to the Trimbos Multidisciplinary Guideline Anxiety Disorders and the Trimbos Multidisciplinary Guideline Depression. The presence of GAD/PD/MDD will be assessed by the and GAD-7, Patient Health Questionnaire, panic module (PHQ-PD), and the PHQ-9 (see next paragraph). Stepped-care has been proven to be effective in older people with anxiety and/or depression.

Stepped-care involves four subsequent treatment steps for anxiety and depression in primary care. A practice nurse mental health (POH-GGZ) of the patient's own general practice guides the patient through the various steps of the program. All participating POH's-GGZ will receive a training of two days about stepped-care, guided self-help and problem solving therapy before start of the intervention. The GP is easily accessible for the POH-GGZ to discuss about a patient if needed. The steps of the program involve: (1) watchful waiting, 6 weeks; (2) bibliotherapy, 6 weeks; (3) Problem Solving Therapy, 6 weeks; and (4) indicated treatment. The patient will proceed to the next step after every 6 weeks in case of persisting complaints. The POH-GGZ will seek for an alternative treatment step if a patient is not motivated for an offered intervention. The intervention, as part of our study, is finished when the patient does not suffer from anxiety/depression anymore, or when the patient still suffers from anxiety/depression and proceeds to step 4.

*Step 1. Watchful waiting.* The first 6 weeks consists of a period of watchful waiting, because it is known that depressive/anxiety symptoms often disappear spontaneously over time. In this 6 week period, the patient will be invited by the POH-GGZ for a first consultation to get familiar with the POH-GGZ. During this introductory consultation the POH-GGZ will shortly inform the patient about depression/anxiety and the stepped-care program. After 6 weeks the POH-GGZ will invite the patient again. The patient will be asked to fill out the GAD-7, PHQ-PD and PHQ-9. In case of persisting anxiety and/or depression the patient will go to step 2.

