*Step 2. Bibliotherapy.* During this step the patient will start with a guided self-help course (based on Lewinsohn's 'Coping with Depression' course). This self-help course is based on cognitive behavioural techniques and takes 6 weeks. The patient will receive a course book and every week, the patient will read about new insights and skills to cope with anxiety and/or depression. The book consists of information and exercises, which the patient can work through at his/her own pace. The POH-GGZ will support the patient by contacting the patient by telephone every two weeks, and by providing extra guidance if necessary. Since many patients of our population will be visual impaired, the POH-GGZ will also receive a digital version of the course to be able to print the text in a large size if necessary. After 6 weeks the POH-GGZ will invite the patient. The POH-GGZ will discuss the current depressive/anxiety symptoms and the patient will be asked to fill out the GAD-7, PHQ-PD and PHQ-9 again. In case of persisting anxiety and/or depression the patient will go to step 3.

*Step 3. Problem Solving Treatment (PST).* PST is a brief cognitive behavioural intervention that focuses on practical skill building, education and managing depressive symptoms. The goal is to achieve a reduction in mental health problems by stimulating an active attitude towards everyday problems. PST will be offered by the POH-GGZ and takes a maximum of 7 sessions at the general practice.

At the end of the PST-course the POH-GGZ will discuss the current depressive/anxiety symptoms and will ask the patient to fill out the GAD-7, PHQ-PD and PHQ-9 again. If a depression and/or anxiety still exists the patient is offered to go to step 4.

*Step 4. Indicated treatment.* The POH-GGZ will discuss the outcomes of the previous treatment steps with the GP if the patient is still suffering from anxiety and/or depression after the preceding steps. The GP will then have a consultation with the patient to assess what would be an appropriate next therapy for the patient (e.g. starting with antidepressants). The GP will then initiate the treatment.

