### 3. Exercise therapy for risk factor impaired functional mobility

Dizzy elderly with the risk factor 'impaired functional mobility' (defined as a TUG score of 20 seconds or more), will receive standardized exercise therapy by a physiotherapist. Earlier research has shown that exercise therapy aiming to improve strength and balance in older people has a positive effect on mobility and reduces rate of falls and risk of falling. The exercise therapy implies training in a group session of one hour twice a week for eight weeks and will focus on strength (including resistance) and balance.

The program starts with 15 minutes warming up exercises in standing and walking with different combinations of head, trunk, arm and leg movements. This will be followed by a circuit training with 8 stations. The patients will perform a two minute exercise at every

station and will perform two laps of the circuit. The stations include the following exercises: standing on foam with eyes closed, standing on foam while flexing the knees and turning the head from side to side, a walking exercise with slalom between cones, knee flexor/extensor training with an ankle cuff, hip abductor/adductor training with an ankle cuff, standing up on toes, and standing on heels. All exercise of the circuit will be individually tailored by performing the exercises with or without extra support to remain standing, varying with the weight of the ankle cuff, standing or walking on heels and toes and standing or jumping on the trampoline. The exercise therapy will end with a cooling down of 10 minutes. The program will be accompanied by music of the group's preference.

No adverse reactions other than musculoskeletal discomfort related to exercise therapy has been described, in particular no fall related injuries occurring during exercise programs have been described.

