### 8.3 Study procedures

#### Questionnaires

If a patient agrees to participate in the study he/she will receive a set of questionnaires. Patients in group A (n = 125) will receive three questionnaires at baseline and at 6 and 12 months follow-up. Patients in the intervention study (group B and C, n = 250) will receive four questionnaires at baseline and at 3, 6 and 12 months follow-up. The questionnaires will be discussed later in this section.

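### Adverse events are recorded only if volunteered or noticed, and scheduled contact differs by arm, so events without a systematic measure are not reliably comparable between groups B and C

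*Protocol*

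**What the plan says.** Section 9.2.1 of the protocol defines an adverse event broadly, as "any undesirable experience occurring to a subject during the study, whether or not considered related to the experimental intervention". The recording rule is narrower: "All adverse events reported spontaneously by the subject or observed by the investigator or his staff will be recorded".

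The trial's regular contact with patients in both arms of the intervention study is by questionnaire. Under section 8.3, groups B and C "will receive four questionnaires at baseline and at 3, 6 and 12 months follow-up". Neither the description of the instruments nor the measurement table in that section contains an adverse-event question.

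Section 5.1 gives group C contacts that group B does not have:

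- **Medication adjustment:** one GP consultation, at which the GP "will stop or withdrawal the FRIDs if the patient agrees".
- **Stepped care:** an introductory consultation, then "After 6 weeks the POH-GGZ will invite the patient again". Step 2 adds support by "contacting the patient by telephone every two weeks" and a closing visit. For step 3, "PST will be offered by the POH-GGZ and takes a maximum of 7 sessions at the general practice". Step 4 is a GP consultation.
- **Exercise therapy:** "training in a group session of one hour twice a week for eight weeks".

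Group B receives usual GP care. Under section 8.3, a random sample of 30 of its patients also gets one additional home visit.

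**The concern.** Under a passive rule, an event enters the record only if the patient has an occasion to mention it or someone is there to notice it. The intervention itself supplies many more such occasions in group C. If those occasions lead to recording, a difference in event counts between B and C mixes true harm with opportunity to report. An excess in C could be an artefact, and a real excess could be dismissed as one.

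The events most exposed are those that these interventions could plausibly cause and that no instrument measures. Section 5.1 itself names musculoskeletal discomfort as the known reaction to exercise. Symptoms after a fall-risk-increasing drug is stopped, changed or reduced, without admission, are the other example; 62% of group C is expected to be eligible for that component.

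This is a rule about data collection. An analysis plan cannot later recover events that nobody asked about.

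**Working it through.** The protocol gives no figure on this point, so there is none to reproduce. The check counts scheduled contacts and then sets the capture methods side by side.

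**Inputs**

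- Expected shares of group C eligible (section 5.1): medication adjustment 0.62, stepped care 0.48, exercise 0.37.
- Contacts for medication adjustment: 1 GP consultation.
- Contacts for exercise: 2 per week × 8 weeks = 16.
- Contacts for stepped care, S. The minimum is 2 (introduction and week-6 visit, with recovery after step 1). The maximum is 2 + 3 telephone calls + 1 visit + 7 problem-solving sessions + 1 GP consultation = 14.
- Group B: 1 extra visit in 30 of 125 patients (section 8.3).

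**Average scheduled contacts per patient**

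Group C = 0.62 × 1 + 0.37 × 16 + 0.48 × S

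| | Medication | Exercise | Stepped care | Total |
|---|---|---|---|---|
| S = 2 | 0.62 | 5.92 | 0.96 | 7.50 |
| S = 14 | 0.62 | 5.92 | 6.72 | 13.26 |

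Group B = 30/125 = 0.24.

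This assumes that every eligible patient attends everything offered. It counts telephone calls as contacts and leaves out the baseline assessment and usual care, which both arms have.

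**Where the contacts fall.** Exercise and stepped care supply (5.92 + 0.96)/7.50 = 92% of the low total and (5.92 + 6.72)/13.26 = 95% of the high total. A patient eligible only for medication adjustment has 1 scheduled contact; an exercise patient has 16. The averages therefore describe a contrast concentrated in the patients eligible for exercise or stepped care.

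**What is and is not captured alike in B and C**

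| Event or outcome | Method | Same in B and C? |
|---|---|---|
| Falls, dizziness episodes | Weekly calendar, 12 months | Yes |
| DHI, PHQ-9, GAD-7, PHQ-PD | Questionnaires at 0, 3, 6, 12 months | Yes |
| EQ-5D-5L | Questionnaires at 0, 6, 12 months | Yes |
| Hospital and nursing home admissions | Medical record, all patients | Yes |
| Consultations | Count from the record | Same method, but the intervention itself adds practice visits in C |
| Other adverse events | Volunteered or observed | Same rule, unequal occasions |

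**From contacts to bias.** With equal true risk, the ratio of recorded events (C to B) equals the ratio of the detection proportions in the two arms. The protocol gives neither proportion. If one assumed, purely for illustration, 20–40% detection in B and 40–50% in C, the ratio would run from 0.40/0.40 = 1.0 to 0.50/0.20 = 2.5, which includes no bias at all. The contact counts show unequal opportunity; they do not give the size of its effect.

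**The case against.** The strongest reply has four parts.

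1. **No adverse-event comparison is promised.** Section 9 deals with recording and with reporting to the ethics committee. Section 10 names no adverse-event analysis, and tabulation may be left to an analysis plan. This stands, and it limits the point: no stated analysis is invalid. It does not remove the point, because the collection rule decides whether any later comparison would be meaningful.

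2. **Much harm-relevant information is collected identically.** This stands. A reader might infer that harms as a whole cannot be compared fairly between arms, or that the section 9.2.1 record is the trial's main safety evidence, since section 9.5 provides for no safety board. The documents do not support either reading. Falls, mood and anxiety scores, quality of life and admissions have a common method. Return of a treated condition may also show partly in the PHQ-9, GAD-7, prescriptions or referrals. The record data are described as counts, however, so that coverage is partial.

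3. **The mechanism is weak for drug withdrawal.** Medication adjustment schedules one visit, at which the change is made, and no later one. For patients with only that component, scheduled contact adds little chance of noticing later symptoms. This stands. Such symptoms remain without a systematic measure in either arm, but the contact imbalance arises mainly from the other two components.

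4. **Contact is not capture.** The extra contacts are with the patient's GP, the practice's mental health nurse and a physiotherapist. The protocol does not say that they are the investigator's staff or must pass events on. The GP's feedback form concerns medication changes. Group B patients also see their GP. This stands too, and it leaves even the direction open. If these professionals report, C may be over-recorded. If they do not, events mentioned to them may never reach the study.

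**Conclusion.** The point holds in limited form. Adverse events recorded under section 9.2.1 that have no systematic measure are not reliably comparable between B and C, because nobody asks about them and scheduled contact is about 7.5 to 13.3 per patient in C against about 0.24 in B. The contact figures rest on the protocol's expected eligibility shares, full attendance, and stepped care ending anywhere between step 1 and the step 4 consultation.

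A reader might go further and infer that event counts in C will be inflated by a stated factor. The documents give no detection rates and do not define who counts as staff, so neither size nor direction can be derived. Falls, dizziness, DHI, anxiety and depression scores, EQ-5D-5L and admissions lie outside the concern. The change is worth making because it is cheap and can only be made while data are being collected.

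**What to change.** - Add one adverse-event item, with identical wording and the same recall period, to the 3-, 6- and 12-month questionnaires that groups B and C already receive.
- State in section 9.2.1 whether GPs, practice nurses and physiotherapists count as staff and whether they must pass events on.
- Base any between-arm comparison of harms on that item and the other identically collected sources: the fall calendar, the questionnaires, and admissions and deaths from the medical record. Section 8.1.2 does not name deaths among the data to be extracted, so they should be added there.
- List spontaneous and staff-observed reports separately, without comparing arms.

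The cost is a small added burden for patients and some extra coding of events. No new visit is needed, and the treatment schedules do not change.
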